This multi-method study consists of a focus group study and an observational prospective study. The ultimate goal of this multi-method study is to provide valuable insight into the severity of psychological consequences, including ASD and PTSD, and the need for a psychological intervention study to prevent PTSD. First, focus groups are held to examine patients’ experiences with injury (and their care). In this way, potential factors related to the development of psychological problems (eg, depressive symptoms) and disorders (eg, anxiety, ASD, and PTSD) can be obtained and taken into account for the observational study (aim 1). Subsequently, an aim of the observational study is to examine the courses of ASD and PTSD (aim 2). In addition, it will be examined which socio-demographic (ie, sex, age, marital status, and education level), clinical (ie, type of trauma, Injury Severity Score (ISS), Glasgow Coma Score, being hospitalized, being treated on the intensive care unit, complications during treatment, and treatment by a medical psychologist or psychiatrist), and psychological variables (eg, anxiety, depressive symptoms, and personality) characterize the courses of ASD and PTSD. Subsequently, a risk profile will be developed to determine which patients are at risk for ASD and/or PTSD (aim 3). Finally, to study the effect(s) of the natural course of ASD symptoms on the development of PTSD, anxiety and depressive symptoms, and QOL across time will be analyzed (aim 4).

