##### Additional Assessments

Socio-demographic information (ie, sex, age, marital status, and education level) will be obtained from patients at baseline. Clinical information, including date of trauma treatment, ISS, type of trauma mechanism (eg, traffic accident or fall), type of injury (eg, fracture), trauma treatment (eg, operation or medication), consult or treatment from medical psychology (yes/no and which type of treatment), hospital stay (yes/no), in case of hospital stay, admission to intensive care unit, and duration of hospital stay will be abstracted from the patients’ medical records. Possible logistic problems will also be recorded.

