#### Observational Study

The patient characteristic will be studied using descriptive statistics. Then, the baseline characteristics (ie, sociodemographic, clinical, and psychological variables) of participants versus nonparticipants, participants who complete versus drop out during follow-up, and participants who are discharged versus being in the hospital after treatment in the shock room will be compared using independent t-tests and Chi-squared tests. Nonnormal continuous data will be analyzed with Mann-Whitney U tests or Fisher’s exact tests.

Repeated measures of latent class analysis will be used to analyze the courses (ie, time is independent variable) of ASD and PTSD (dependent variables). Moreover, to examine if these different courses of ASD and PTSD (independent variable) could be characterized by socio-demographic (eg, sex, age, education level, and living situation) and clinical (eg, type of trauma, ISS, Glasgow Coma Score, being hospitalized, being treated on the intensive care unit, complications during treatment, and treated by a medical psychologist or psychiatrist), and psychological (eg, anxiety, depressive symptoms, and personality) variables (dependent variables). As a result, each class will represent a different course of ASD and PTSD. By focusing on the characteristics of the different classes, a risk profile will, consequently, be developed to determine which patients are at risk for ASD or PTSD. Sociodemographic and clinical variables are examined as moderating effect, while psychological variables are studied as mediating effects.

Linear mixed models, repeated measures, will be used to examine the effect of ASD (independent variable) on PTSD, anxiety and depressive symptoms, and QOL domains (dependent variables) over time (see Table 2).

The ISS, type of injury and type of trauma mechanism (eg, traffic accident or fall) will be used as covariates. 

**Table 2 table2:** Overview of statistical analysis

Baseline analysis and aims^a^	Independent variables	Dependent variables	Analyses
Patient characteristics	Sociodemographics	N/A^b^	Frequencies Descriptives
	Clinical variables	N/A	Frequencies Descriptives
	Psychological variables	N/A	Frequencies Descriptives
Comparison of patient characteristics	Participants versus nonparticipant	Sociodemographics Clinical variables Psychological variables	Continuous data: Independent t-test, Mann-Whitney U Categorical data: Chi-squared, Fishers’ exact test

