	Completers versus noncompleters	Sociodemographics Clinical variables Psychological variables	Continuous data: Independent t-test, Mann-Whitney U Categorical data: Chi-squared, Fishers’ exact test
	Participants being discharged versus being in the hospital	Sociodemographics Clinical variables Psychological variables	Continuous data: Independent t-test, Mann-Whitney U Categorical data: Chi-squared, Fishers’ exact test
Aim 2: Course of ASD and PTSD	Time	ASD^c^ PTSD^d^	Repeated measures, latent class analysis
Aim 3: Risk profile	ASD PTSD	Sociodemographics Clinical variables Psychological	Repeated measures, latent class analysis
Aim 4: Effect of ASD	ASD	PTSD Anxiety Depressive symptoms QOL^e^	Linear Mixed models, repeated measures

^a^The dependent and independent variables for aim 1 could not be provided because this aim focuses on qualitative data.

^b^N/A: Not applicable.

^c^ASD: acute stress disorder.

^d^PTSD: posttraumatic stress disorder.

^e^QOL: quality of life.

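### The covariates stated for the aim 4 model of the effect of ASD are injury variables only, so the estimate is open to confounding by sex, age, education level and marital status

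*Protocol article*

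**What the plan says.** The Introduction states aim 4 as an effect question: "to study the effect(s) of the natural course of ASD symptoms on the development of PTSD", together with anxiety and depressive symptoms and quality of life. Under Statistical Analysis, Observational Study, the model is: "Linear mixed models, repeated measures, will be used to examine the effect of ASD (independent variable) on PTSD" and on the other outcomes over time. A separate one-sentence paragraph directly after it gives the adjustment: "The ISS, type of injury and type of trauma mechanism (eg, traffic accident or fall) will be used as covariates".

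On demographics, the article says three things:

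- Additional Assessments: "Socio-demographic information (ie, sex, age, marital status, and education level) will be obtained from patients at baseline".
- Introduction, for the ASD and PTSD courses: "it will be examined which socio-demographic (ie, sex, age, marital status, and education level), clinical" and psychological variables characterise them. The results feed a risk profile for ASD and/or PTSD (aim 3). The Statistical Analysis section repeats this with sex, age, education level and living situation as examples.
- End of the latent-class and risk-profile paragraph, before the mixed model is introduced: "Sociodemographic and clinical variables are examined as moderating effect, while psychological variables are studied as mediating effects".

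No section names sex, age, education level or marital status as a covariate in the aim 4 model.

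**The concern.** Patients with and without ASD are not randomised groups, so an estimated effect of ASD depends on what it is adjusted for. A variable that relates both to having ASD and to later PTSD, distress or quality of life will shift the estimate if it is left out. The article treats the four demographic variables as candidates for such a link: it asks whether they characterise the course of ASD, which is the aim 4 exposure, and of PTSD, which is an aim 4 outcome. Sex and age cannot be consequences of ASD, and all four variables are recorded at baseline.

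If the model is fitted with the three stated covariates, any demographic difference between the ASD groups that also predicts the outcome, and that the injury variables do not capture, is reported as part of the effect of ASD.

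**Working it through.** **Plan's own figures.** The Sample Size Calculation gives N=300 and an effect size of 0.4. The printed inputs do not lead to 300 under a plain two-group comparison: with an equal split, a two-sided 5% test and 80% power, the total is 198. The article also cites Monte Carlo simulations that it does not show, so this does not prove 300 wrong, and the present point does not depend on it. Below, 300 and 0.4 serve only as yardsticks, with 0.4 read as SD units (an assumption).

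**Inputs.** The article gives no association between demographics and ASD or the outcomes. Everything in steps 1 to 3 is therefore assumed: 35% women, the ASD rates by sex, the outcome difference by sex, and an ASD share of about 25% (75 v 225).

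**Step 1: bias from leaving out sex.**
Bias = [P(female | ASD) − P(female | no ASD)] × sex difference in outcome (SD).

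Example with ASD in 35% of women and 20% of men:
- P(ASD) = 0.35×0.35 + 0.65×0.20 = 0.2525
- P(female | ASD) = 0.1225/0.2525 = 0.485
- P(female | no ASD) = 0.2275/0.7475 = 0.304
- Difference = 0.181; with a sex difference of 0.4 SD, bias = 0.181×0.4 = 0.072 SD

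| ASD, women v men | Sex difference (SD) | Prevalence difference | Bias (SD) | Share of 0.4 |
|---|---|---|---|---|
| 30% v 22% | 0.3 | 0.098 | 0.029 | 7% |
| 35% v 20% | 0.4 | 0.181 | 0.072 | 18% |
| 40% v 17% | 0.5 | 0.279 | 0.139 | 35% |

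If either association is zero, the bias is zero.

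**Step 2: false-positive rate if ASD has no effect.**
Noncentrality = bias × √(75×225/300) = 7.5 × bias. Rejection rate = P(Z > 1.96 − 7.5b) + P(Z < −1.96 − 7.5b).
- b = 0.029: 7.5b = 0.22, rate about 5.5%
- b = 0.072: 7.5b = 0.54, rate about 8.4%
- b = 0.139: 7.5b = 1.04, rate about 18%

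**Step 3: four omitted binary variables, by simulation.** N=300, true ASD effect 0, 2,000 replicates per setting.

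| Odds ratio for ASD, each | Effect on outcome, each (SD) | Apparent ASD effect, unadjusted (SD) | False positives, unadjusted | False positives, adjusted |
|---|---|---|---|---|
| 1.0 | 0.3 | 0.00 | 6.0% | 5.3% |
| 1.5 | 0.2 | 0.08 | 9.7% | 5.2% |
| 2.0 | 0.3 | 0.18 | 27% | 4.5% |
| 2.0 | 0.0 | 0.01 | 5.5% | 5.4% |

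With the four variables in the model, the mean estimate was within 0.005 SD of zero in every setting.

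**Step 4: precision.** This is a minor benefit. At a true effect of 0.4 SD the noncentrality is 7.5×0.4 = 3.0 and power is 85%. If demographics explain 5%, 10% or 15% of outcome variance, it becomes 3.0/√(1−R²) and power is 87%, 89% or 90%.

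**Limits.** These are single-time comparisons. They ignore the repeated measures and the three stated covariates, which could absorb part of a demographic difference.

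**The case against.** **The moderators may already be in the aim 4 model.** This is the strongest objection. Moderation and mediation presuppose an exposure-outcome effect, and aim 4 is where the article has one. If the moderator sentence reaches the mixed models, demographic main effects would normally enter with the interactions. The text does allow this reading, but the sentence closes the latent-class paragraph and nothing ties it to aim 4. It also covers clinical variables, yet ISS and trauma mechanism are named again as covariates, while the demographics are not. Testing whether an effect differs by subgroup is not a commitment to an adjusted main estimate. What stands is that the article should say which model the moderators enter.

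**A reader might infer that the ASD effect is confounded.** The article does not support this. It will examine whether demographics characterise the courses and does not assert that they do.

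**A reader might take the aim 4 row of Table 2 ("Aim 4: Effect of ASD") as proof that demographics are excluded,** since ASD is its only independent variable. That fails: Table 2 lists no covariates in any row, not even the three named in the text. Nor does the covariate sentence say that the list is exhaustive.

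**The adjustment set may be left to an analysis plan.** Silence on covariates could be excused that way. Here the article states a specific set, and that stated choice is what is questioned.

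**The study is exploratory, and its stated use is partly prognostic.** This is fair. An association not adjusted for demographics can still help to identify patients at risk. The aim of informing a future intervention study belongs to the whole project, not to aim 4 alone. But aim 4 is worded as an effect, and being exploratory does not remove confounding.

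**Conclusion.** The point holds in a limited form. The covariates stated after the aim 4 mixed model are injury variables only, and the article nowhere commits to adjusting for four baseline demographic variables that it examines in relation to the courses of both ASD and PTSD. The estimated effect of ASD is therefore open to confounding by patient demographics, of unknown size and direction. The range of 0.03 to 0.14 SD for sex alone rests wholly on assumed inputs and shows what is possible, not what is expected. The reason to act is that a stated analysis choice leaves an avoidable source of bias which data already being collected can address.

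**What to change.** In Statistical Analysis, Observational Study, extend the covariate sentence for the aim 4 models to: ISS, type of injury, type of trauma mechanism, sex, age (continuous), education level and marital status, entered as main effects. Report the three-covariate model alongside, so that readers see how far the ASD estimate moves. State which model the moderation terms belong to.

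The cost is wording and a few degrees of freedom at N=300: if education and marital status have three levels each (an assumption), 1+1+2+2 = 6 terms per model. Covariate-by-time interactions are optional and dearer: with five time points treated as categorical, 6×4 = 24 further terms. Confounding by factors outside the list may remain, so the adjusted estimate should not be presented as free of bias.

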## Results

Data collection and analysis for the focus group study are completed. Results will be reported in 2018. Enrollment of participants for the observational study began in November 2016. Data collection will be completed by the end of 2018. The study results will then be reported in 2019.

## Discussion

This is the first multi-method study in trauma patients that examines psychological consequences after injury, using both a qualitative focus group study design as well as an observational prospective design. In the focus group study, the aim was to interview patients about their experiences with the injury, treatment, and rehabilitation. Since it is unknown if and in what way patients’ experiences contribute to the development of psychological problems and disorders. The observational study will examine the course of ASD and PTSD, as ASD after injury is less studied and it is unknown how ASD and PTSD develop over time up to 12 months after injury. Moreover, as a result of all outcome measures, a risk profile of patients may be determined to predict which patients are at risk for developing ASD or PTSD. Altogether, this study will provide information concerning which patients to include in further research that focuses on psychological intervention.

Several factors related to the design and execution must be taken into account. First, response bias may occur in the focus group study. Patients may decline participation because they are not interested in discussing their experiences, or it might be too confronting to talk about their experiences and psychological problems. Second, it is known that the population of trauma patients has a broad variety of trauma mechanisms and injuries. Therefore, it might be difficult to generalize to the whole trauma population. However, concerning the observational study, almost all trauma patients being treated in the shock room will be included from two different Level-1 trauma centers so data saturation can be reached. These centers are located in different provinces and cities in The Netherlands. Therefore, a representative population in the observational study can be included. Third, patients with severe injuries might be less capable to complete the baseline questionnaire almost directly after injury due to being treated at the intensive care unit. Patients will, therefore, be asked to fill in the date of completing the questionnaire and if they needed any help. Then, the time between injury and measurement can be analyzed. This provides information on what time severely injured patients are capable to complete the baseline questionnaire.

In conclusion, this study is exploratory in nature and it will contribute to the need for information on psychological consequences after injury. Then, awareness in clinicians about the consequences can be created so they are able to act more effective and patient-oriented care can be provided.

## Appendix

Multimedia Appendix 1 DSM-5 Diagnostic criteria for acute stress disorder (ASD).

Multimedia Appendix 2 DSM-5 Diagnostic criteria for posttraumatic stress disorder (PTSD).

## Abbreviations

ASD: acute stress disorder
DSM: Diagnostic and Statistical Manual of Mental Disorders
HADS: Hospital Anxiety and Depression Scale
IES-R: Impact of Event Scale-Revised
ISS: Injury Severity Score
NEO-FFI: NEO Five-Factor Inventory
PTSD: posttraumatic stress disorder
QOL: quality of life
STAI: State Trait Anxiety Inventory
WHOQOL-Bref: World Health Organization Quality of Life assessment instrument-Bref
